**Figure 1. fig1-20552076221129068:**
[figure not shown]
Study design.

At the enrollment (T1), patients will fill out the baseline questionnaires
collecting patient demographic information, and assessing their perceived
quality of life. The perceived quality of life is again measured at the end of
the intervention (T2).

Each patient will be followed for three–five days, depending on the standardized
care. During this period, health care quality measures, including health quality
measures, blood pressure, oxygenation and heart rate, and pain, are collected
for both groups two times a day. Blood pressure, oxygenation, and heart rate are
measured in all in-patients, recorded daily (standard procedure) and recorded on
a progression chart. In the intervention group, blood pressure, oxygenation, and
heart rate measures are stored electronically and the CDSS is used to flag
deviations from the standard, and alert the treating clinician. In the control
group, the standard progression chart is used as per hospital protocol. The
treating clinician is autonomous to decide to step up or modify antihypertensive
treatment. Pain is measured in all in-patients on daily basis, two times a day
(standard procedure), and recorded on a progression chart. In the intervention
group, the pain level is stored electronically and CDSS is used to flag and
alert the treating clinician on pain levels identified above anticipated. In the
control group, the standard progression chart is used as per hospital protocol.
The treating clinician is autonomous to decide to step up or modify analgetic
treatment.

The participating clinicians will be asked to evaluate the clinical usability and
provide answers on their acceptance of the CDSS system five times during the
study (after the first iteration, after half a year, after the first year, after
a year and a half, and after the last iteration).

### Participants and recruitment

The proposed study intends to recruit two distinct samples: patients and
clinicians. The patient sample will be composed of patients admitted to vascular
surgery or thoracic surgery wards for an elective (non-emergency) procedure.
Patients will need to be aged 18 years or above and willing to participate in
the study. Exclusion criteria include emergency patients, patients already
enrolled in other studies, patients with dementia, patients with special needs
or appointed guardians, and patients allocated to an intensive step-down unit
and/or regimen. The sample of clinicians will be composed of clinicians
participating in a grand round routine within the vascular surgery or the
thoracic surgery ward. Again, only employees aged 18 years or above, who will
have signed a consent form, will be eligible to participate in the study.

There will be a pool of 400 eligible participants (200 per ward) available for
inclusion in this study. Vascular and Thoracic Surgery Wards at the University
Clinical Center Maribor treat over 4000 individuals annually and it is estimated
that roughly 1400 individuals meet the inclusion criteria. However, based on the
fact that, in general, at most 30% of participants (or less) consent to the
clinical study,^
39
^ we assume that the final number of subjects willing to participate will
be much lower. Regarding sample size requirements for the present study, public
registries of clinical trials were reviewed. ClinicalTrials.gov returned 12
studies using the keywords “Vascular Diseases,” “CDSS,” and “randomized clinical
trial,” while ISRCTN and EU Clinical Trials Registers returned no studies under
the same conditions. These studies primarily focused on Stroke Prevention, CVD
Risk Factor Control, and Hypertension. These studies differed substantially in
the number of participants enrolled, from 40 to 400,000 participants per study.
Considering the tertiary settings, the studies involved between 40 and 400
participants, with an average of 80 patients. In this study, 100 patients
treated for Vascular Diseases will be enrolled in the study. Only one study was
found on ClinicalTrials.gov using keywords “Thoracic Diseases,” “CDSS,” and
“randomized clinical trial” involving 47 participants, while ISRCTN and EU
Clinical Trials Registers returned no studies under the same conditions. In this
study, 100 patients treated for Thoracic Diseases will be enrolled.
Additionally, we also performed calculations using the G*Power software.
Patient-related analyses will predominantly be based on the ANOVA repeated
measures statistical test with the within-between interaction (two groups, two
measurements). As we hypothesize a small effect size
(*f* *=* 0.10) and intend to use a
conventional significance threshold and power (α = 0.05, 1-β = 0.80), the total
sample size needed to detect the effects is 200 participants.

The clinicians will be included in the study with the within-subjects design,
whereby they will fill out the questionnaires five times during the study
period. As such, we performed the sample size calculation in the G*Power
software, choosing the Repeated Measures ANOVA test as the statistical test,
entering a medium effect size (*f* = 0.25), and choosing a
conventional significance threshold and power (α = 0.05, 1-β = 0.80). Such
calculations suggest that at least 21 clinicians must be recruited overall.

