## Methods

### Study design

The proposed study is designed as an experimental, prospective randomized
controlled clinical trial. Participants of the study, that is patients with
vascular or thoracic diseases, and clinicians, will be recruited at the regional
university clinical center. The study will be carried out in one-week intervals
over a two-year period, with one-week wash-out period between each iteration.
Clinicians will be participating in the study over the whole two-year period,
while patients will be participating only during their stay at the hospital.
During wash-out period, the CDSS and SAHR are not used in the departments. The
study will be carried out and reported on individually for the two cohorts. At
the end of the study, the results will be cross-compared to assess possible
generalizability across surgery settings.

Patients admitted to vascular or thoracic surgery wards for an elective
(non-emergency) procedure will be screened for eligibility regarding the
inclusion and exclusion criteria. Eligible participants will then be informed
about the study characteristics and asked to fill out an informed consent form.
Those who will consent to participate in the study will participate for five
days (one week) and will be randomized by the clinicians into: Intervention Group (CDSS delivered by SAHR is actively used), andControl Group (CDSS is not used; instead, only standard workflow and
progression charts are utilized).

Blinding will be achieved by handling the same tools during the grand rounds.
However, in the control group, the robot and tablet will not provide any
information to clinicians. Blinding will be furthermore achieved by adhering to
the usual workflow and paper progression charts with all patients in both
groups. The study procedure is outlined in Figure 1.

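### The 80% power belongs to all 200 patients together, but the study is to be reported ward by ward (100 each), and the article does not say which unit the tests use

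*Protocol article*

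**What the plan says.** Three statements in the Methods of the protocol article bear on the unit of analysis.

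- **Study design:** the "study will be carried out and reported on individually for the two cohorts". The results are then compared between the cohorts at the end, to judge whether they generalise across surgery settings.
- **Participants and recruitment, enrolment:** there are separate targets for the wards. "In this study, 100 patients" with vascular disease are to be enrolled, and likewise in this "study, 100 patients treated for Thoracic Diseases will be enrolled". Each target is supported by the sizes of registered studies.
- **Participants and recruitment, power calculation:** "As we hypothesize a small effect size" (f = 0.10), with alpha 0.05 and power 0.80, for a repeated-measures ANOVA interaction with two groups and two measurements. The total "sample size needed to detect the effects is 200 participants". For clinicians (f = 0.25, five measurements), "calculations suggest that at least 21 clinicians must be recruited overall".

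The Abstract describes 200 patients randomised to two groups that are then compared, and about 22 clinicians. The two analysis sections, for patient-related and clinician-related outcomes, name one type of analysis per hypothesis. Neither mentions a split by ward or a ward factor.

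**The concern.** A power statement holds only for the analysis it was computed for. Here it was computed for both wards together, while Study design makes the single ward, half that size, the unit in which the study is run and reported. No power is given for one ward, and no ward-adjusted pooled analysis is described.

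What is at stake is how a ward result will be read. With significance declared at p below .05, a null result in one ward would be set against a stated 80% power that it does not have. The planned comparison between wards is exposed as well: if each ward is tested alone with about even odds of success, one significant and one non-significant ward is a likely result even when the effect is the same in both. The Discussion describes the samples of patients and clinicians as large enough; the calculation supports that for the pooled sample only.

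**Working it through.** **Inputs from the article (Participants and recruitment).** Patients: f = 0.10, alpha = 0.05, two groups, two measurements, total 200, with 100 per ward. Clinicians: f = 0.25, alpha = 0.05, five measurements, minimum 21 overall. The Abstract gives about 22 clinicians.

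**Assumptions.** The article does not state the correlation between repeated measurements (rho), sphericity, or the allocation ratio. I take rho = 0.5, sphericity and 1:1 allocation. The first two are supported by the fact that they reproduce both published sizes.

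**Formula.** Noncentral F test in the form used by G*Power, with N subjects and m measurements:

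lambda = f² × N × m / (1 − rho)

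Degrees of freedom are (1, N − 2) for the patient interaction and (4, 4(N − 1)) for the clinicians' time effect.

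**Step 1: reproduce the published figures.**

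- Patients, N = 200: lambda = 0.01 × 200 × 2 / 0.5 = 8, df (1, 198), power 80.4%. N = 198 gives 79.97%, so 200 is the smallest even total.
- Clinicians, N = 21: lambda = 0.0625 × 21 × 5 / 0.5 = 13.125, df (4, 80), power 81.6%. N = 20 gives 79.3%, so 21 is the minimum.

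Both published numbers are reproduced exactly, and both are pooled numbers.

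**Step 2: the same patient test in one ward.**

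- N = 100: lambda = 0.01 × 100 × 2 / 0.5 = 4, df (1, 98), power 50.8%.
- Effect detectable with 80% power at N = 100: f = 0.141.
- 80% power at f = 0.10 in each ward would take 200 patients per ward, 400 in total. The 200 per ward mentioned in the article is the pool of eligible patients, not the enrolment.

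**Step 3: sensitivity to the unstated correlation.**

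| rho | Total needed for 80% | Power, N = 200 | Power, N = 100 |
|---|---|---|---|
| 0.3 | 278 | 66.2% | 38.8% |
| 0.5 | 200 | 80.4% | 50.8% |
| 0.6 | 160 | 88.2% | 60.0% |
| 0.7 | 120 | 95.3% | 72.5% |
| 0.8 | 82 | 99.4% | 87.9% |

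Only the row for 0.5 agrees with the published 200. The other rows show what would happen if the real correlation differed; they do not describe the calculation behind the plan.

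**Step 4: comparing the two wards.** If f = 0.10 in both wards and each is tested alone, both are significant with probability 0.508² = 0.26. Exactly one is significant with probability 2 × 0.508 × 0.492 = 0.50.

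**Step 5: clinicians, illustration only.** The article gives no split by ward. With an assumed 11 per ward, lambda = 0.0625 × 11 × 5 / 0.5 = 6.875, df (4, 40), power 47.9%. With 10, power is 43.3%.

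**Step 6: cost of a ward factor.** For 21 clinicians, adding a two-level ward factor changes the power of the time effect from 81.6% to 81.5%.

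**The case against.** **The pooled reading is open.** The Abstract compares two randomised groups of 200 in all, the sample-size text speaks of a total and an overall number, and the analysis sections name no ward split. Separate reporting does not exclude a pooled test. This stands. A reader might infer that every test in the trial will be run at half the planned size; the document does not say so, and the loss of power is conditional on the Study design sentence governing the tests.

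**The two cohorts might be patients and clinicians.** The sentence follows one about those two samples. This does not stand. Patients and clinicians answer different instruments, so comparing their results could not show generalisability across surgery settings, and enrolment is fixed ward by ward.

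**The 51% covers one analysis.** This stands. It is the power of an ANOVA with two groups and two time points, which the analysis section uses for quality of life (H3). A reader might extend it to H2, but those measures are analysed with growth curves on twice-daily data, and no power is stated for that analysis, pooled or by ward.

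**The clinician figure is weak.** This also stands. The two separate ANOVAs planned for clinicians are one for acceptance and one for usability, not one per ward, and the 11/11 split is assumed. The 48% therefore cannot be stated as the power of the H1 analysis, although H1 concerns the outcomes that the Measures section treats as primary.

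**The article already limits its claims.** It speaks of possible generalisability and of the difficulty of general conclusions. That is a caution about external validity; it does not correct a power figure attached to the wrong unit.

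**Conclusion.** The concern holds as an inconsistency between the unit in which the study is reported and the unit for which it is powered. The published 200 and 21 are correct for pooled analyses, so the calculation itself is not wrong.

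If Study design governs the tests, the H3 ANOVA has about 51% power per ward instead of 80%, and 80% is available only from about f = 0.14. This rests on rho = 0.5, which is back-solved rather than stated, on 1:1 allocation, and on all 100 patients per ward being analysed. The article excludes incomplete cases, so any loss would lower the figure. Nothing is shown for H2. For H1 the per-ward figures, 48% with 11 clinicians and 43% with 10, only illustrate what a ward split would do.

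It should be settled before the data are analysed, because it decides which result answers the hypotheses.

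**What to change.** Reconcile Study design with Participants and recruitment. State that the pooled analysis of all 200 patients, and of all clinicians, with ward as a fixed factor, decides H1 to H3. Report ward-specific results as estimates with 95% confidence intervals and without a significance verdict of their own. The existing sample-size statement for the ANOVAs then matches the analysis.

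If separate ward reports are to stay confirmatory, restate the power instead: about 51% per ward for the H3 ANOVA at f = 0.10, with the assumed correlation given, and for clinicians the lower power that follows from the actual number in each ward.

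Either way the change is to wording, with no added patients. The price is the loss of a stand-alone significance verdict per ward under the first option, or a less favourable stated power under the second.

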### Measures

Testing the primary hypotheses will require the measurement of several outcomes,
namely clinical usability and acceptance of the CDSS system from the clinicians’
perspective. To evaluate the clinical usability of the CDSS system, a System
Usability Scale (SUS)^40,41^ will be used. SUS is an often-used measure for
assessing the subjective usability of systems and products. Several studies
proved its psychometric quality in several languages. It consists of 10 items
(e.g. “I thought the system was easy to use.”), which are answered on a
five-point scale from one (strongly disagree) to five (strongly agree).^
42
^

To evaluate the acceptance of the CDSS system, a unified theory of acceptance and
use of technology and its extension will be used (UTAUT^
43
^ and UTAUT2^
44
^). The UTAUT model proposes four constructs regarding technology
acceptance, that is performance expectancy, effort expectancy, social influence,
and facilitating conditions. The extended version of the model, UTAUT2,
incorporates additional three constructs, that is hedonic motivation, price
value, and habit.^
44
^ As there is no one specific questionnaire based on the UTAUT and UTAUT2
models, but rather they are developed for specific studies and technologies
assessed, this approach will be followed also in the present study in the
co-creation phase, where the questionnaire will be defined in detail.

The secondary objective of the study is to evaluate the possible impact of the
CDSS on health quality measures and quality of life of patients. To assess
health quality measures, blood pressure, oxygenation and heart rate will be
recorded daily, two times per day for all patients. In addition, pain levels
will be assessed as part of the health quality measures. The visual analog scale
(VAS) is a validated, subjective measure for acute and chronic pain. Scores are
recorded by making a handwritten mark on a 10-cm line that represents a
continuum between “no pain” and “worst pain.”^
45
^ VAS was evaluated with no statistically significant difference observed
between the paper and laptop computer platforms. Thus, VAS can be adapted to
digital and paper formats.

Finally, to evaluate the potential impact of CDSS on quality of life the EQ-5D-3L instrument^
46
^ is used in both groups of patients. The EQ-5D-3L's descriptive system
comprises the following five dimensions: mobility, self-care, usual activities,
pain/discomfort, and anxiety/depression. The EQ-5D-3L tool essentially consists
of two pages: the EQ-5D descriptive system and the EQ visual analog scale (EQ VAS).^
47
^ The Slovenian version was validated by Prevolnik-Rupel with a
representative sample of 3000 adults.^
48
^

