^ Furthermore, the newly developed CDSS will provide intuitive visualizations
of patients’ health-related data, including EHRs, health quality measures (i.e.
pain, blood pressure, oxygenation, and heart rate), patient-reported data, and
patient-reported outcomes. The health data will be structured in an interoperable
HL7-FHIR format.^
31
^ The real-time access during the grand round routine is ensured with
speech-enabled user interfaces delivered via a tablet attached to the socially
assistive humanoid robot (SAHR), Pepper.^
32
^ While the uptake of SAHR in clinical practice is so far limited,^
33
^ and to our best knowledge, there are no studies on the integration of CDSSs
and social robotics yet, such innovative delivery could have several important
benefits. In particular, it could make the use of a CDSS more effortless for
clinicians (e.g. due to the robot being capable of movement, carrying the tablet,
and offering assistance with queries in natural language) as well as more
satisfactory and engaging for all involved stakeholders including
patients.^34,35^ It could serve as an enabler of real-time querying and
visualization of patient data.^
36
^ Adding human characteristics to the CDSS could contribute to higher trust in
the system.^33,37,38^

We hypothesize that clinicians will accept the CDSS and recognize its clinical
usability (H1). The use of CDSS will have a positive impact on health quality
measures (H2) and the quality of life of patients (H3). In addition to our primary
hypotheses, we aim to explore the impact of real-time access to the extended
clinical background on diagnostic and treatment workflows for patients with vascular
and thoracic diseases and conditions (R1).

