## Plan of analysis

### Preliminary analyses

We will use the IBM SPSS Statistics 26 program for statistical analysis. In the
first step, we will clean the dataset and exclude participants with missing data
on any of the measurement points and within questionnaires, with more than 20%
of missing values. We will also perform basic psychometric analyses of the
questionnaires, namely the factor or other appropriate analyses to evaluate the
internal structure of the questionnaires and analysis of reliability as internal
consistency (coefficient α) and calculate the scores in accordance with the
scoring instructions.

In the next step, we will perform basic descriptive analyses (means and standard
deviations) and check the assumptions of the chosen statistical tests (such as
the normality of the distribution assumption). This step will be followed by
inferential tests, whereby results with a *p*-value below .05
will be considered statistically significant.

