### Analyses of patient-related outcomes

The impact of CDSS use on the first patient-related outcome, that is health
quality measures (H2), will primarily be analyzed with growth curve
analyses.

The impact of CDSS use on the second patient-related outcome, that is perceived
quality of life (H3), will primarily be analyzed with repeated-measure analysis
of variance (ANOVA), with time as the within-subjects factor (T1 and T2; see
Figure 1).
Significant results will be followed up with pairwise post-hoc tests using the
correction to adjust for multiple testing. All results will be accompanied by
effect sizes.

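### H2 and H3 are primary in the Introduction but secondary in Measures, and no error control is stated across the patient outcomes, each tested at .05

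*Protocol article*

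**What the plan says.** **Status of the hypotheses.** The Introduction states H1 (clinicians accept the system and find it usable), then H2 with "The use of CDSS will have a positive impact on health quality" measures, and H3 on quality of life. It next turns to the exploratory question R1 with the words "In addition to our primary" hypotheses. All three are thus primary there, and only R1 is exploratory.

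The Measures section opens with "Testing the primary hypotheses will require the measurement of several outcomes" and names only clinical usability and acceptance from the clinicians' side. It then brings in health quality measures and quality of life as follows: "The secondary objective of the study is to evaluate the possible impact of the" system on them.

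**Testing rule.** Preliminary analyses refers to "inferential tests, whereby results with a *p*-value below .05", which "will be considered statistically significant". Under Analyses of patient-related outcomes, H2 is analysed with growth curves and H3 with a repeated-measures ANOVA over T1 and T2. The same section adds "Significant results will be followed up with pairwise post-hoc tests using the" correction for multiple testing, whose method is not named. The clinician section repeats that sentence for its two ANOVAs.

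**Cohorts and sample size.** Study design says the vascular and thoracic cohorts are reported individually and compared at the end. Participants and recruitment derives a total of 200 patients from one group-by-time interaction test, and at least 21 clinicians from a separate within-subjects calculation.

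**The concern.** The two statements of status are both current text and cannot both hold. If the Introduction governs, the randomised comparison of patients carries the trial through H2 and H3. If Measures governs, the trial is decided by how clinicians' ratings change over time, and the randomised comparison is supporting evidence.

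The testing rule makes this ambiguity costly. H2 is one hypothesis with four measured outcomes, H3 adds at least one more, and the article does not say how many must succeed, or in what order, before benefit to patients is claimed. The promised correction acts below the level of the outcome. For H3, with two arms and two times, it has almost nothing to correct. It does not apply across outcomes or wards. A reader of the final report could not attach an error rate to the statement that H2 was supported.

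**Working it through.** **1. The plan's own sample sizes.** Each is for a single test at α = 0.05 with power 0.80. The within-person correlation is not stated, so ρ = 0.5 is assumed. The noncentrality is λ = f²·N·m/(1 − ρ).

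- Patients: f = 0.10, two groups, m = 2. λ = 0.01 × 200 × 2 / 0.5 = 8 on 1 and 198 df, giving power 0.804. N = 198 gives 0.7997, so 200 is reproduced. (At ρ = 0.3 the required N would be 278; at ρ = 0.7, 120.)
- Clinicians: f = 0.25, m = 5. λ = 0.0625 × 21 × 5 / 0.5 = 13.125 on 4 and 80 df, giving power 0.816. N = 20 gives 0.793, so 21 is reproduced.
- Patient test in one ward of 100: λ = 0.01 × 100 × 2 / 0.5 = 4, giving power 0.51.

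The article states no error rate across tests, so there is no such figure to reproduce.

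**2. Counting the patient-outcome tests.** The outcomes come from Measures.

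- H2: blood pressure, oxygenation, heart rate and pain, so 4.
- H2 and H3 pooled over wards: 4 + 1 = 5.
- Each tested in both wards, which is one reading of Study design: 5 × 2 = 10.

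These are face-value counts. Analysing systolic and diastolic pressure separately, or the EQ-5D descriptive system and the EQ VAS separately, would raise them.

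**3. Chance of at least one false positive**, with all nulls true and independent tests, is 1 − 0.95^k:

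| Tests | k | 1 − 0.95^k |
|---|---|---|
| H2 outcomes | 4 | 1 − 0.8145 = 18.5% |
| H2 + H3, pooled | 5 | 1 − 0.7738 = 22.6% |
| H2 + H3, per ward | 10 | 1 − 0.5987 = 40.1% |

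**4. Allowing for correlation.** Outcomes measured in the same patients are unlikely to be independent. Simulating ten equally correlated two-sided z tests (400,000 sets) gives 35%, 29% and 21% at correlations of 0.3, 0.5 and 0.7. The correlations are assumptions. Applying one correlation to all ten tests probably lowers the result too far, because the two wards contain different patients and tests across wards are not correlated through shared patients.

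**5. Which analysis the 200 belongs to.** The calculation is for two groups and two measurements. Of the patient analyses described, only H3 (T1 and T2) has that form; H2 uses repeated daily readings in growth curves.

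**The case against.** Several points against a broader criticism are sound.

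- A reader might infer that a spurious positive result is likely. The figures do not support that: all are below one half, they require every null to be true, and they fall with correlation.
- A reader might count ten or more tests as fixed by the plan. They are not. Ten requires reading the per-cohort reporting as separate confirmatory tests, whereas the sample size treats the 200 as one total. A range from four to ten is all the text supports.
- A reader might add the two clinician ANOVAs, reaching 12 tests and 46%. Those are time effects in a different sample with its own sample size, answering a different question. They do not belong in the same error family.
- A reader might say that no correction is planned at all. One is, for post-hoc tests, and it matters for clinicians, whose five occasions give 5 × 4 / 2 = 10 pairwise comparisons.
- Sizing the patient sample on a patient analysis is not itself inconsistent, and it does not make that outcome primary.
- The article nowhere says that any one vital sign suffices for H2. How secondary outcomes combine is commonly left to an analysis plan, which is not shown. If Measures governs, unadjusted secondary tests with restrained claims are common practice.

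The last point is the strongest, but it does not dispose of the matter. The article is not silent: it sets the threshold and says where correction applies. An analysis plan also cannot inherit the status of H2 and H3 from a protocol that gives two answers.

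**Conclusion.** The point holds in a limited form. The Introduction and Measures contradict each other on whether H2 and H3 are primary, so the document does not say which result decides the trial. As written, the testing rule leaves the patient outcomes without control of error across outcomes: 18.5% for the four H2 outcomes, about 23% for five pooled tests and about 40% for ten, if all nulls hold and tests are independent. With an assumed correlation of 0.5, ten tests give about 29%. All are well above 5%.

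The ten-test figures depend on the per-cohort reading of Study design, which the article leaves open. The documents do not support the stronger conclusions that a false positive is more likely than not, or that EQ-5D must be the primary outcome.

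**What to change.** 1. Give H1, H2 and H3 one consistent status in the Introduction and in Measures.
2. Treat H1 as a separate clinician question with its own error rate.
3. Name one deciding patient outcome, or a fixed testing order. The two-group, two-measurement sample size matches the EQ-5D analysis, but the choice is the sponsor's.
4. Test the four H2 outcomes as one family with Holm adjustment in the pooled 200, and state that H2 is supported only by adjusted results.
5. Say in Study design whether the cohort-specific results are confirmatory or descriptive. Descriptive fits the sample size, which covers only the total; one ward of 100 has about 51% power for the planned interaction test at the assumed correlation of 0.5.

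The changes are to wording in the protocol and any analysis plan, though items 3 and 5 need real decisions. The cost is stricter thresholds within H2: under Holm the ordered p-values are compared with 0.05/4 = 0.0125, 0.05/3 = 0.0167, 0.05/2 = 0.025 and 0.05, stopping at the first failure. N = 200 and α = 0.05 for the deciding test can stay.
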